### Intervention

The help-seeking intervention draws upon two models of behaviour change – the Information-Motivation-Behavioural Skills Model (IMB) and the Theory of Planned Behaviour (TpB). The IMB model is a well-validated, comprehensive health behaviour change framework that has been used in schools, particularly for HIV education and prevention [20]. The TpB is a health behaviour change framework that has been used extensively to guide experimental health intervention trials [21]. In this study, the help-seeking activities to be trialled provide students with information about how to seek help and from whom (Information), investigate participants’ psychological barriers to help-seeking (Beliefs, Intentions), investigate risky behaviours associated with alcohol use and mental health problems (Symptom levels), and provide opportunities and videos for skill rehearsal (Behavioural skills) which, according to our composite model, will lead to increased intention to seek help and actual help-seeking (Behavioural outcome).

The intervention will consist of five interactive classroom activities run over two school periods (average period is 75 minutes), plus a booster session 1 month later (to reiterate key messages and help students gain practical experience by applying the help-seeking skills they have learnt), delivered by an experienced external facilitator with the assistance of the regular classroom teacher. The rationale for the addition of a booster session is based on feedback and data from our pilot investigations, as well as research indicating the importance of booster sessions in terms of enhancing and maintaining treatment effects [22]. Activities will cover (1) recognising when a friend needs help (vignettes about poor mental health and risky drinking), (2) what types of helpers are available, (3) myths and facts about substance use and mental health, (4) identifying and overcoming barriers to professional help-seeking, (5) assisting a friend to access help, and (6) accessing reliable sources of help (see Table 1).

**Table 1 Tab1:** Summary of activities included in the intervention

Activity	Description
Ranking for risk	*Know* mental health can fluctuate from ‘good’ to ‘poor’ in the course of a day or over a lifetime the difference between poor mental health and mental illness relates to duration and severity of symptoms *Understand* people perceive risk differently depending on their experiences, values and beliefs a drug experience will differ depending on the drug that is taken, the person who takes it and where they take it talk about suicide must be taken seriously and the friend at risk must be referred on to an adult *Do* a student is able to assess short-term and long-term risk in a hypothetical situation identify ‘red flags’ (e.g. risk of harm to self or to others, change in behaviour, etc.)
Myths and facts	*Know* what the research states in relation to the selected ‘myths’ and ‘facts *Understand* that stigma and misunderstandings relating to mental health issues and substance use do exist and these may act as barriers for young people thinking about seeking help *Do* correct misperceptions held by peers around mental health and substance use
Under construction	*Know* the brain is still developing until the age of 25 years *Understand* what happens to the adolescent brain and the body when alcohol is consumed *Do* a student is able to make informed choices about drinking alcohol as an adolescent
Helpers	*Know* the range of helpers that are available within and outside of school *Understand* the barriers that may stop a person from seeking help the difference between professional confidentiality and duty of care *Do* a student is able to ask questions to confirm what information will be passed on, and what will be kept confidential when speaking to a helper
Helping Jason	*Know* how to have an effective health-seeking conversation with a friend *Understand* that encouraging a friend to seek help may take time, and repeated efforts that it is more effective to ask questions than to tell someone what to do *Do* a student is able to plan a help-seeking conversation with a friend
Booster	*Know* key information from the course (see previous activities) *Understand* key information from the course (see previous activities) *Do* ‘sell’ a health-promoting message to a friend (in poster form) tasks as specified in the above five ‘do’ categories

### Recruitment process

Recruitment for the trial began in August 2013. Emails providing information about the programme opportunity and inviting expressions of interest from schools were sent to all Catholic, independent, and state schools within 50 km of Melbourne’s CBD with a year-9 cohort of between 40 and 250 students. Schools were required to obtain consent forms signed by the students’ parent/guardian for them to participate in the study, returning a minimum of 60 % positive consents of year-9 students and guardians to be eligible to participate in the trial. In order to maximise return of consent forms, each school principal assigned a staff member to the MAKINGtheLINK project in order to take responsibility for their collection. In addition, the research team ran two presentations for year-9 students to explain why participation in the survey was important, provided clear instructions about where and when to return consent forms, and provided extra copies of forms where required. After these initial steps were taken, contacts at each school emailed or telephoned parents to follow up with them about the consent forms.

In spite of these efforts, we were unable to obtain the required sample size at four of the seven schools that had agreed to participate by December 2013. In order to increase participation rates, and supported by the Department of Education and Early Childhood Development, a passive/opt-out consent process was adopted from 2014 onwards where parents were no longer required to opt in to the research, and students could make an informed choice as to whether they wanted to participate. Under this process, students are assured that participation is optional and that they will not be penalised for choosing not to participate, and are required to check the ‘consent’ box before completing the online survey. Parents are informed of the research at least 1 month in advance and can opt out of the research trial by contacting the school if they do not want their children involved.

All consenting students subsequently undergo baseline testing during class prior to intervention delivery. Intervention schools then receive the programme in their regular class time. Participants will be re-tested the week following the intervention or at an equivalent time for the control schools (6 weeks post baseline). Follow-up assessments will also be completed online during class at 6 and 12 months post baseline. All students will be provided with information on how to seek help for substance use, depression and other problems from a range of resources and services at the completion of the surveys. Figure 2 shows the SPIRIT diagram for the trial procedure.

**Fig. 2 Fig2:**
[figure not shown]
SPIRIT diagram. SPIRIT, Standard Protocol Items: Recommendations for Interventional Trials

All information in the survey will be de-identified and confidential, and the records will be kept securely for 5 years at the research centre (Turning Point) after which time they will be destroyed. However, if students report high scores on a screen for depression the researchers will notify the student welfare coordinator (SWC) who will contact the child to check that they are safe and refer for assistance as appropriate. Any student who becomes upset while completing the surveys can stop at any time. The researcher will be available to provide debriefing, and the student will be encouraged to talk to their parents or one of their teachers. They will also be provided with contact details for services, if necessary.

### Measures

In addition to demographic information (age, gender, postcode, language spoken at home, living arrangements, parental occupation, country of birth), the following measures will be administered.

#### Mental health symptoms

Levels of stress, anxiety and depression symptoms will be measured by the 21-item version of the Depression Anxiety Stress Scales (DASS-21) [23]. The DASS-21 consists of 21 statements that measure symptoms of depression, anxiety and stress that are experienced in the past week (seven statements per scale). Each statement is rated on a 4-point scale (0 = not at all, 3 = very much, or most of the time). Scores for each item are summed to indicate participants’ levels of depression, anxiety or stress. The DASS-21 has good discriminant and concurrent validity, sound convergent reliability with other measures of depression and anxiety (e.g. [23, 24]), and has been used successfully in previous studies with adolescent samples [25].

#### Alcohol use

Alcohol use will be measured by adapting questions from the Australian Secondary School Students Alcohol and Drug (ASSAD) Survey [26]. This will allow for comparison between use in the current sample and a large-scale representative group of Australian secondary school students. Participants self-report whether they have ever drunk alcohol or drank in the past year, frequency of drinking and drinks consumed in the past 7 days. Alcohol-related harms will be assessed using questions from two large adolescent longitudinal studies, the Adolescent Temperament Project [27] and the International Youth Development Study [28]. Over 10 questions, participants are asked to indicate on a 3-point Likert scale (0 = never, 1 = once or twice, 2 = more often) the number of times in the last 6 months that their alcohol use had caused them specific problems (e.g. get so drunk they were sick or passed out; have trouble at home, work or school the next day; get injured or have an accident; be unable to remember what happened the night before).

#### Help-seeking

*Intention to seek help* will be measured with the General Help Seeking Questionnaire (GSHQ-V) [29]. This 15-item questionnaire requires participants to indicate how likely they would be to seek help for alcohol or depression from a number of sources (e.g. boyfriend/girlfriend, friend, parent, teacher, GP) rated on a 5-point (1 = very unlikely to 5 = very likely) scale. The problem-type and the help-sources of the GHSQ-V will be modified to ensure that the measure is relevant to the particular context and research questions of the current study in line with recommendations by Wilson and colleagues [30].

*Prior help-seeking behaviour* will be assessed using supplementary questions from the GHSQ-V. Young people will be asked if they have ever sought help from a professional helper (e.g. school counsellor, counsellor, GP, psychologist, psychiatrist, nurse, alcohol and drug worker) and to indicate whether it was for an alcohol, drug, mental health or ‘other’ problem and how helpful this was (rated 1 = very unhelpful to 5 = very helpful). Actual help-seeking in the past 6 months will be assessed with a simplified version of the Actual Help Seeking Questionnaire (AHSQ) [31], and adapted to include substance use and mental health (four items): (1) Have you sought help or advice for an alcohol-related problem in the past 6 months? (2) If yes, who from? (3) Have you sought help or advice for depression or another emotional problem in the past 6 months? (4) If yes, who from? Facilitation of help-seeking for a friend will also be assessed at each time point using a modified version of these tools.

*Confidence to seek help* will be measured using a 5-point Likert scale, where 1 = not confident at all to 5 = very confident: How confident are you to seek help if you had an alcohol or drug problem*?* How confident are you to seek help if you had depression or another emotional problem?

*Confidence to seek help for a peer* will be measured using a 5-point Likert scale, where 1 = not confident at all to 5 = very confident: How confident are you to assist a friend to seek help if they had an alcohol or drug problem? How confident are you to assist a friend seek help if they had depression or another emotional problem?

#### Psychological barriers

*Beliefs about seeking professional help* will be measured using a brief version of the Barriers to Adolescents Seeking Help questionnaire (BASH-B) [32], which comprises 11 barriers to seeking help rated on a 6-point scale from ‘strongly agree’ to ‘strongly disagree’.

*Stigma* will be measured using the Depression Stigma Scale and the Social Distance Scale reported in Yap and colleagues [33]. Mental illness vignettes relevant to alcohol misuse and depression will also be included followed by the questions: ‘How much do you agree with the statement “Sarah needs help”’, ‘How much do you agree with the statement “Sarah would benefit from professional help”’, ‘How confident would you feel to help Sarah see a professional?’ and ‘If you were behaving like Sarah, what do you think could be wrong with you?’ The first four questions are scored on a Likert scale and the fifth is a free-text response.

### Blinding

Schools will be unaware of each school’s allocation until after they have provided consent. Participating individuals and their parents will be unaware of whether they have been allocated to the intervention or control group until after the first data collection point.

### Statistical analysis

The research staff will co-ordinate all appropriate data management and cleaning prior to analysis. Data on screening, refusals and dropout will be coded and reported as per Consolidated Standards of Reporting Trials (CONSORT) guidelines for participant flow through the trial (see Fig. 3). A description of the baseline characteristics of schools and of individuals who participate in the two intervention arms will be compiled using descriptive statistics such as mean and standard deviation, median and interquartile range, and percentages.

**Fig. 3 Fig3:**
[figure not shown]
Consolidated Standards of Reporting Trials (CONSORT) flow diagram of progress through the phases of the MAKINGtheLINK trial

In order to evaluate the main aim of the study, which is to examine the association between participation in the help-seeking programme (control versus intervention arm) and actual help-seeking behaviour at 12 months post intervention, logistic regression analyses will be undertaken testing for group differences between help-seeking behaviour as measured by the AHSQ. In a secondary analysis, gender, depression and anxiety scores, reported alcohol problems, and any characteristics of schools or participants that are imbalanced to a large extent at baseline, will be included in an extended logistic regression model for help-seeking behaviour in addition to the control/intervention arm indicator variable.

For secondary aims, the outcomes are measured by continuous variables, and as such linear regression analysis will be used to compare the two study arms with the primary analysis comprising models with treatment indicator and the baseline value of the outcome score, i.e. analysis of covariance. Secondary analyses will adjust for imbalanced characteristics in the same way as for the primary analysis. All analyses will utilise robust standard errors to adjust for clustering by school.

Each analysis described above will be conducted using participants with all necessary data for that analysis, according to the intention-to-treat principle. Characteristics of participants who were lost to follow-up and who completed follow-up will be compared. Analyses will be repeated using all participants on the basis of multiple imputation involving responses at all four time points to impute for missing values.

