## Methods/design

### Study design

The study (see Fig. 1) is a randomised controlled trial (RCT) with schools as clusters and individual students as participants, and will follow the Standard Protocol Items: Recommendations for Interventional Trials (SPIRIT) Statement for reporting trial protocols (see Additional file 1 for checklist) [17]. All consenting participants will be assessed at four time points: baseline, 6 weeks post baseline, 6 months post baseline and 12 months post baseline. Participants from the control schools will be assessed on equivalent dates at the four time points.

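### The primary logistic model omits baseline help-seeking, which the trial measures: the test stays valid but gives up precision and protection against chance imbalance among 22 schools

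*Protocol article*

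**What the plan says.** All of the modelling is in the Statistical analysis section of the protocol article.

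- **Primary outcome:** "logistic regression analyses will be undertaken testing for group differences between help-seeking behaviour as measured by the AHSQ". No covariate is named.
- **Extended model, a secondary analysis of the same outcome:** gender, depression and anxiety scores, alcohol problems and "any characteristics of schools or participants that are imbalanced to a large extent at baseline". These "will be included in an extended logistic regression model for help-seeking behaviour in addition to the control/intervention arm indicator variable". The natural reading is that the primary model contains the arm and nothing else.
- **Secondary outcomes:** linear "models with treatment indicator and the baseline value of the outcome score, i.e. analysis of covariance". Here the baseline value belongs to the main model.
- **Clustering:** "All analyses will utilise robust standard errors to adjust for clustering by school".

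The baseline measure exists. Under Study design, "All consenting participants will be assessed at four time points: baseline", followed by 6 weeks, 6 months and 12 months. The Help-seeking part of Measures lists a simplified AHSQ with two yes/no items (an alcohol problem; depression or another emotional problem) over a 6-month recall. The Recruitment process section puts baseline testing before delivery. The Blinding section keeps students and parents unaware of allocation until after the first data collection. That the AHSQ is part of the baseline survey follows from reading these sections together; the SPIRIT figure is not shown.

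**The concern.** The plan uses the baseline value of the outcome wherever the outcome is secondary, and not for the outcome on which the trial will be judged. No reason is given.

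With about 11 schools per arm, stratified only on a two-level ICSEA score, the arms can differ by chance in prior help-seeking. A baseline covariate removes whatever part of the student-level and school-level variation persists to 12 months. An arm-only model leaves that part in the error term.

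The extended model does not repair this. Baseline help-seeking is not on its fixed list. It could enter only under a rule that is undefined (how large is large?), is applied after the baseline data are seen, and selects on observed imbalance rather than on prognostic value. Even then the result is a secondary analysis.

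**Working it through.** **1. The plan's own sample size (Sample size calculation section).** Inputs: difference 6.4%, pooled SD 18.8%, two-sided alpha 5%, power 80%, ICC 0.05, 51 analysed students per school.

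- n per arm before clustering = 2 × (1.960 + 0.842)² × 0.188² / 0.064² = 135.5, rounded up to 136.
- Design effect = 1 + (51 − 1) × 0.05 = 3.5.
- 136 × 3.5 = 476 per arm; 476 / 51 = 9.3, so 10 schools; 2 × 10 × 51 = 1020; 1020 / 0.75 = 1360.

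Every figure reproduces. The calculation takes no credit for a baseline covariate. At 510 per arm (10 schools) its power is 82.8%.

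**2. Chance baseline imbalance between arms.** SD of the difference = √[2 × p(1 − p) × 3.5 / (11 × 51)], with the planning ICC assumed to apply to baseline help-seeking. The prevalence p is assumed, because the article gives none for formal plus informal help.

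| p | SD | 95% range |
|---|---|---|
| 0.6% (GP rate used in planning) | 0.0086 | ±1.7 points |
| 10% | 0.0335 | ±6.6 points |
| 20% | 0.0447 | ±8.8 points |
| 30% | 0.0512 | ±10.0 points |

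From 10% upward the range exceeds the 6.4-point target. Such an imbalance carries through to 12 months only in proportion to the baseline-to-follow-up association.

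**3. Simple approximation of the gain.** Residual variance is scaled by 1 − r², where r is an assumed baseline-to-12-month correlation. From the unrounded 135.5 × 3.5 ≈ 474:

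| r | n per arm | power at 510 per arm |
|---|---|---|
| 0.2 | 456 | 84.3% |
| 0.4 | 399 | 88.7% |
| 0.5 | 356 | 91.9% |

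**4. Simulated cluster logistic models.** Setting: 22 schools, assumed rates 21% versus 30%, fitted with and without the baseline item. The two larger sets used a school SD of 0.42 on the logit scale and Mancl-DeRouen variance with a t reference. Phi is the student-level baseline-to-follow-up correlation. Persistence is the correlation of a school's effect at baseline with its effect at follow-up.

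| phi (about) | persistence | power, arm only → with baseline | trials |
|---|---|---|---|
| 0.27 | full | 55% → 71% | 2,500 |
| 0.29 | full | 67% → 82% | 1,000 |
| 0.31 | full | 61% → 78% | 500 |
| 0.29 | half | 66% → 73% | 1,000 |
| 0.31 | half | 63% → 72% | 500 |
| 0.29 | none | 64% → 65% | 1,000 |
| 0.31 | none | 70% → 71% | 500 |
| 0.11 | full | 52% → 58% | 2,500 |
| 0.10 | full | 55% → 61% | 1,000 |
| 0.10 | half | 55% → 58% | 1,000 |
| 0.10 | none | 56% → 57% | 1,000 |

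The unadjusted levels differ between sets, so the gains are what to compare: 15 to 17 points at full persistence with phi about 0.3, 7 to 9 at half, and about 1 at none.

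**5. Other assumed rates.**

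- 2% versus 8%: 97% both ways.
- 5% versus 11.4%: 81% both ways at phi 0.04; 86% → 91% at phi 0.18.
- 20% versus 30%, 10 schools per arm, phi about 0.46, school-level correlation 0.8: 46% → 68%. A stronger association than phi 0.3 would therefore give a larger gain.

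**The case against.** The case for leaving the model alone is substantial, and most of it stands.

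- **Validity.** Randomisation makes the arm-only comparison valid, and its standard error already carries the chance variation in step 2. A reader might infer that the primary result would be biased; the documents do not support that.
- **Consistency with planning.** The sample size assumes no baseline adjustment, and 22 schools are to be recruited against 20 required. A reader might infer that the omission leaves the trial below its planned power; it does not. The low unadjusted power in step 4 comes from the assumed rates, not from the missing covariate.
- **Size.** The largest gains need school effects that persist fully. At the 0.6% planning rate about 7 of 1,122 students (22 × 51) would be positive at baseline, so the covariate would be almost constant. The article expects higher rates for formal plus informal help but gives no figure.
- **Prognostic strength.** It is tempting to call prior help-seeking the strongest predictor of later help-seeking. Nothing in the article shows this. The two 6-month recall windows do not overlap, and the Discussion accepts that some students will have no problem during the trial.
- **The extended model.** It would be wrong to say that baseline help-seeking can never enter; the imbalance clause can admit it. That protection is secondary and data-driven.
- **Detail for an analysis plan.** Covariates are often settled there. But the article states both models, lists the extended covariates, and specifies baseline adjustment for the secondary outcomes. This is a stated choice rather than an omitted detail.

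**Conclusion.** The point holds as one of efficiency and consistency, and is worth changing. As the article reads, the primary model is arm-only although the baseline value is collected and the same section uses baseline values for every secondary outcome.

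The cost is lost precision and exposure to chance imbalance. The imbalance range is about ±6.6 points at an assumed 10% prevalence and ±8.8 at 20%, against the 6.4-point target. That comparison is indicative only, since the article expects both the prevalence and the effect to be larger than the GP figures.

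At 21% versus 30% the power gain runs from about 0 with no school persistence to about 16 points with phi about 0.3 and full persistence. It is also near 0 if baseline help-seeking is very rare. The article does not show where in this range the trial lies, so no single figure should be quoted as the loss. None of the simulated settings lost power from adjusting.

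**What to change.** Prespecify baseline AHSQ help-seeking (the alcohol and emotional-problem items) as a covariate in the primary logistic model and keep it in the extended model. Retain school-robust standard errors. Replace the imbalance-triggered rule with a covariate list fixed before outcomes are compared by arm.

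No new data are needed, but there are two costs to plan for:

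- **Missing baseline items.** The main analysis uses students with all necessary data, so a student missing a baseline item would drop out. State how this is handled, for example by a missing indicator or by the multiple imputation already planned.
- **Change of estimand scale.** The adjusted odds ratio is conditional on the covariate. Report a marginal risk difference alongside it, which also matches the difference in proportions used for planning.

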**Fig. 1 Fig1:**

Schematic illustration of the research design

Twenty-two Victorian secondary schools will be recruited for the study. Schools will be randomly allocated to either receive the intervention immediately or to form a waitlist control group and receive the intervention after completion of the fourth survey. Randomisation will be stratified by the school’s Index of Community Socio-Educational Advantage (ICSEA) score, with two strata defined as <1000 (‘disadvantaged’) and 1000+ (‘advantaged’). The random allocation list will be generated using Stata statistical software, Release 12 (StataCorp, College Station, TX, USA: 2011) with random block sizes of 2 or 4 within each strata.

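### In the secondary adjusted models, covariates beyond the four named ones are picked by observed baseline imbalance rather than prognostic value, while the ICSEA stratum is in no model

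*Protocol article*

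**What the plan says.** The Statistical analysis section has two layers.

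- **Main analyses.** For the primary outcome, "logistic regression analyses will be undertaken testing for group differences between help-seeking behaviour as measured by the AHSQ"; no covariate is named. For the secondary outcomes, "models with treatment indicator and the baseline value of the outcome score, i.e. analysis of covariance".
- **Adjusted analyses.** For the primary outcome, the extended model opens with "In a secondary analysis, gender, depression and anxiety scores, reported alcohol problems", and then adds "any characteristics of schools or participants that are imbalanced to a large extent at baseline". For the secondary outcomes, "Secondary analyses will adjust for imbalanced characteristics in the same way as for the primary analysis". I take this to carry the four named covariates across as well.

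Clustering is handled in one sentence: "All analyses will utilise robust standard errors to adjust for clustering by school". Under Study design, "Twenty-two Victorian secondary schools will be recruited for the study"; they are randomised within two ICSEA strata, split at 1000, in blocks of 2 or 4. The ICSEA stratum is not named as a covariate anywhere. The baseline value of help-seeking is not named in either model for the primary outcome.

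**The concern.** A covariate is worth adjusting for when it predicts the outcome. Imbalance is a different property. A variable that differs between arms but is unrelated to help-seeking adds only noise, and a prognostic variable that happens to be balanced is passed over. ICSEA shows the second problem: stratification balances the strata by design, so the rule is unlikely to pick them up, although the Discussion treats school disadvantage as a possible predictor of help-seeking outcomes.

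The part of the covariate set that follows from this rule is settled only once the arms have been compared at baseline. With so few schools, school-level characteristics can differ noticeably by chance alone, and each one added draws on limited between-school information. If the adjusted and main results then differ, a reader cannot tell a prognostic correction from the effect of a model chosen by chance imbalance.

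**Working it through.** **Inputs.** From the protocol: 22 schools, cluster size for analysis 51, ICC 0.05, two-sided 5 % level, 80 % power, difference 6.4 % with pooled SD 18.8 %. Inferred: 11 schools per arm, from even block sizes; incomplete blocks could shift this slightly. Assumed, because the protocol gives neither: 3 to 10 independent candidate school characteristics, and a large-imbalance cut-off of 0.5 to 0.8 SD.

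**The plan's own figure.** The protocol gives no figure for imbalance, but its sample size reproduces. Students per arm before clustering: 2 × (0.188 × (1.96 + 0.84) / 0.064)² ≈ 135.5, so 136. Design effect: 1 + (51 − 1) × 0.05 = 3.5. Then 136 × 3.5 = 476; 476 / 51 = 9.33, so 10 schools per arm; 20 × 51 = 1020; 1020 / 0.75 = 1360. The point below does not change the sample size.

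**Chance imbalance of a school-level characteristic.** The SD of the standardised difference is √(2/11) = 0.426.

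- P(|difference| > 0.5) = P(|Z| > 0.5/0.426 = 1.17) = 24 %
- P(|difference| > 0.8) = P(|Z| > 0.8/0.426 = 1.88) = 6 %

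With 10 schools per arm these become 26 % and 7 %.

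**Chance that at least one enters**, 1 − (1 − p)^K for K independent candidates:

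| K (assumed) | Expected number > 0.5 SD | At least one > 0.5 SD | Expected number > 0.8 SD | At least one > 0.8 SD |
|---|---|---|---|---|
| 3 | 0.72 | 56 % | 0.18 | 17 % |
| 4 | 0.96 | 67 % | 0.24 | 22 % |
| 6 | 1.45 | 81 % | 0.36 | 31 % |
| 10 | 2.41 | 94 % | 0.61 | 47 % |

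**Participant-level characteristics.** With ICC 0.05 and 51 students per school the SD is √(2 × 3.5 / (11 × 51)) = 0.112. By chance, 2.5 % exceed 0.25 SD and almost none exceed 0.5 SD. Chance entry is therefore a school-level matter.

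**Degrees of freedom.** Before adjustment there are 22 − 2 = 20 between-school degrees of freedom, and each school-level covariate takes one. The t critical value is 2.09 at 20, 2.11 at 17 and 2.13 at 15, so the loss itself is small for one or two covariates.

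**Error rate.** A simulation under the null used 22 schools of 51, ICC 0.05, 4000 runs and a linear approximation on cluster means. The school covariates were unrelated to the outcome and were selected by observed imbalance. The robust variance carried only the factor 22/21. Rejection rates at the nominal 5 % level:

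| K | Cut-off (SD) | Unadjusted, normal | Selected model, normal | Unadjusted, t | Selected model, t |
|---|---|---|---|---|---|
| 3 | 0.5 | 6.9 % | 7.7 % | 5.3 % | 6.2 % |
| 3 | 0.8 | 6.3 % | 6.5 % | 4.9 % | 5.1 % |
| 6 | 0.5 | 7.6 % | 9.7 % | 6.2 % | 7.7 % |
| 6 | 0.8 | 7.6 % | 8.5 % | 6.0 % | 6.7 % |
| 10 | 0.5 | 7.1 % | 11.0 % | 5.7 % | 8.7 % |
| 10 | 0.8 | 7.8 % | 9.0 % | 6.0 % | 7.2 % |

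The Monte Carlo standard error is about √(0.07 × 0.93 / 4000) = 0.4 percentage points. When one of 6 candidates explained half of the between-school variance (cut-off 0.5, normal critical values), the rate went from 6.4 % to 7.2 %. The unadjusted excess under normal critical values comes from using robust standard errors with few clusters. The further rise comes with the selected covariates; the simulation does not separate their number from the way they were selected.

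**The case against.** The strongest reply has four parts.

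- **It touches no main analysis.** This stands. A reader might infer that the primary conclusion depends on covariates chosen after seeing the data. It does not: the rule sits in an analysis labelled secondary, four of its covariates are fixed in advance, and selection uses baseline data, not outcomes.
- **The text requires a large imbalance.** This also stands. A reader might infer that many school variables will enter. That would need a low cut-off or a long candidate list, and the protocol gives neither. It names few school characteristics: ICSEA, which is stratified, and sector and year-9 size in the eligibility criteria. For three candidates, about 0.7 are expected beyond 0.5 SD and 0.2 beyond 0.8 SD.
- **Imbalance among participants need not be chance.** Schools are randomised, but from 2014 students consent by ticking a box before the online survey. The Blinding section keeps schools unaware of allocation only until they have consented, so staff may know the arm before students join. Adjusting for a large participant imbalance could then be a sensible check. This has some force. It is limited because students and parents stay unaware until after the first data collection, and because, under Sample, schools do not learn their programme year until consent forms are in. A labelled sensitivity analysis can keep the check.
- **Candidate lists and cut-offs belong in the analysis plan.** Agreed, and their absence from a journal article is not the point here. The protocol states a selection rule. A later cut-off would make it reproducible, but covariates would still be chosen by arm difference.

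**Conclusion.** The point holds for the secondary, adjusted analyses of the primary and secondary outcomes, and only there. Imbalance is a poor criterion for choosing covariates, and the protocol's fixed elements leave out two better candidates: the ICSEA stratum, and, for the primary outcome, baseline help-seeking. Either could still come in if it met the imbalance rule, but neither is assured a place.

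With 3 to 10 candidate school characteristics, the chance that at least one enters through chance imbalance is 56 % to 94 % at a 0.5 SD cut-off and 17 % to 47 % at 0.8 SD. The effect on error control runs from nothing detectable (three candidates, 0.8 SD) to about 11 % rejection (ten candidates, 0.5 SD, normal critical values). These ranges rest on about 11 schools per arm, independent normal characteristics, equal cluster sizes, a linear approximation to the logistic model, and the assumed candidate counts and cut-offs.

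**What to change.** Remove the imbalance rule in both places and state one extended model, fixed before the arms are compared, for the primary and all secondary outcomes: arm, baseline value of the outcome, ICSEA stratum, gender, baseline DASS-21 depression and anxiety scores, and the baseline alcohol-problem score. Show imbalances in the table of baseline characteristics that is already planned. If adjustment for a large participant imbalance is still wanted because participation may have been selective, label it a further sensitivity analysis.

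The cost is a change of wording. The variables belong to measures the protocol already administers or to the randomisation itself, and the sample size is unchanged. The ICSEA stratum uses one between-school degree of freedom, known in advance. The downside is that an unforeseen imbalance no longer enters the main adjusted model. The change does not cure the modest excess error of uncorrected robust standard errors with 22 clusters, which is a separate matter.
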